## Abstract

**Introduction:**

Women undergoing cesarean section frequently report postpartum pain from the surgical procedure, which may be related to functional mobility and cardiorespiratory physiological variables. Transcutaneous electrical nerve stimulation (TENS) and low-level laser therapy (LLLT) photobiomodulation are electrophysical agents used for analgesic purposes in post-cesarean. However, the combined effect of these interventions and their impact on functional performance and cardiorespiratory physiological variables in this population is not known. This study aims to evaluate the effect of TENS combined with LLLT photobiomodulation on pain, functional performance, and behavior of cardiorespiratory variables and compare it with the effects of TENS alone in women during postpartum after cesarean section.

**Methods:**

This is a protocol of a randomized clinical trial that will be conducted at Divino Amor Maternity Hospital (Rio Grande do Norte, Brazil). A total of 88 patients undergoing cesarean section will be distributed in four groups: TENS combined with LLLT photobiomodulation, TENS alone, placebo, and control. The patients included in the study will be evaluated at three time-points: assessment 1 (8–12 hours postpartum), assessment 2 (20–24 hours postpartum), and assessment 3 (44–48 hours postpartum). Data will encompass sociodemographic and clinical information, pain assessment, functional performance, and cardiorespiratory physiological variables (systemic arterial pressure, heart and respiratory rates, and oxygen saturation). The combined intervention group will follow the protocol of two sessions with low-intensity TENS (30 min, 100 Hz, and 75 µs), with electrodes above and below the cesarean incision, and LLLT photobiomodulation (660 nm, 2 J per point, and 100 mW), without touching the cesarean incision. The TENS alone group will follow the same low-intensity TENS protocol used in the combined intervention. Interventions (combined and isolated) will be delivered after completion of assessments 1 and 2.

**Brazilian Registry of Clinical Trials number:**

RBR-9pjd2n3.

## Introduction

The post-cesarean section period is characterized by the presence of complaints such as pain in the abdominal region and limited movements, especially in the first 24 hours after birth [1–3]. Pain in the cesarean incision region is considered post-cesarean morbidity for the mother and infant, characterized as postsurgical pain that may be challenging to recover from. This pain is related to the inflammatory phase of the tissue repair process, which can lead to difficulties in positioning the infant for breastfeeding, caring for the newborn, and performing activities such as sitting, standing, walking, and intimate hygiene [4,5].

Scientific studies identify therapeutic resources as interventions for analgesia, evaluating the possible correlation between pain scores and functional capacity and cardiorespiratory physiological variables (blood pressure, heart and respiratory rates, and oxygen saturation) post-intervention [6,7]. In the literature, transcutaneous electrical nerve stimulation (TENS) [1,8] and photobiomodulation with low-level laser therapy (LLLT) [9,10] are non-pharmacological resources that promote analgesia in the immediate postpartum period after cesarean section.

TENS is a non-invasive, safe, and low-cost treatment modality that uses electrical currents of different frequencies distributed through electrodes placed on the skin surface. The effectiveness of TENS analgesia relates to the gate theory and the activation of the endogenous opioid system [1,11]. In turn, LLLT photobiomodulation utilizes photons in non-thermal irradiance to stimulate biological activity, increasing the production of endogenous opioid neurotransmitters, adenosine triphosphate, anti-inflammatory cytokines, and local angiogenesis, in addition to improving thermal pain. This therapy activates numerous intracellular signaling pathways and alters the affinity of transcription factors related to cell proliferation, survival, tissue repair, and regeneration [9].

In another clinical trial, 90 women post-cesarean were distributed in two groups (TENS and control). For the TENS group, high-frequency, low-intensity TENS (30 min, 100 Hz, 75 μs, sensory threshold, and segmental application) was applied in the immediate post-cesarean period, distributed in two sessions with a 24-hour interval between them, and electrodes placed above and below the cesarean incision. The results showed reduced complaints of pain in the abdominal region associated with the incision and postpartum uterine contractions [1]. Thus, TENS is recommended to improve pain in patients undergoing cesarean section, allowing better execution of activities that require movement in the acute postsurgical phase [1,11,12]. Furthermore, in addition to contributing to functional capacity after cesarean section, a Cochrane review observed that TENS may also reduce heart and respiratory rates [7].

A study verified the analgesic effects of LLLT photobiomodulation in 88 women after cesarean section, randomly distributed in four groups (intervention with 2 J, and intervention with 4 J, placebo, and control). Two sessions of LLLT photobiomodulation (660 nm) were applied, the first at 8–12 hours and the second at 20–24 hours postpartum. The patients reported reduced pain in the cesarean incision after intervention and a perception of global improvement using the Perception of Global Change Scale. According to the authors, the LLLT photobiomodulation with 2 J presented a larger effect size than the other groups [9].

TENS and LLLT photobiomodulation are non-invasive resources and alone can promote analgesia when applied in the first post-cesarean days. Furthermore, they can modify functional mobility and cardiorespiratory physiological variables, such as blood pressure, heart and respiratory rates, and oxygen saturation. However, no studies were found in the literature that verified the effects of combined therapy of these resources in post-cesarean women and how this combined therapy could act on cardiorespiratory physiological variables and functional performance in the target audience of future research. It is important that the physiotherapist performs a procedure that addresses the main complaints, considering the patient’s clinical condition. Thus, the hypothesis of this study is that therapy with TENS combined with LLLT photobiomodulation promotes improvement in functional performance and alters the behavior of cardiorespiratory physiological variables through reduced pain in the cesarean incision in the first post-cesarean days and thus strengthen evidence-based physiotherapy, using scientifically proven physiotherapeutic resources in clinical practice, stimulating the realization of new work related to the subject. The assessed outcomes will encompass pain, functional capacity, and the behavior of cardiorespiratory physiological variables after the intervention.

### Objectives

#### Primary objective.

This study aims to analyze the effect of TENS combined with LLLT photobiomodulation on pain outcomes in women after cesarean section.

#### Secondary objective.

This study aims to evaluate the influence of TENS combined with LLLT photobiomodulation on the outcomes functional capacity, systemic arterial pressure, respiratory and heart rates, oxygen saturation.

## Materials and methods

This randomized controlled clinical trial will be conducted at Divino Amor Maternity Hospital (Rio Grande do Norte, Brazil), and patients will be recruited according to the convenience of admission for cesarean birth and distributed into one of the 4 study groups (TENS alone, TENS combined photobiomodulation LLLT, Placebo or Control). This Study, the recruitment started in the July 2023 and not has been completed, the estimate to data collection be completed is august 2025, and results are expected decision-makers in resource allocation for improved care for this population, aiming to obtain insights into the most effective recuperation in postpartum.

To sample calculation, the study sample was the result of a probabilistic sampling process. For each group, the sample number was 17 volunteers, adding 20% of sample losses, the final number for each group was 22 volunteers. Thus, the sample size was 88 participants, based on the degree of pain in the surgical incision region (according to the numeric pain scale [NPS], graded from 0 to 10, and a reduction of 2 points in the pain score) and variable standard deviation for each group of 1.5. The alpha error was 0.05, the test power was 80% [9,13].

Eligibility criteria will encompass women within 8–12 hours post-cesarean birth; only woman habitual risk pregnancy; presence of pain NPS ≥ 3 in the cesarean incision region; no clinical or obstetric complications; no infectious process; undergoing drug treatment (anti-inflammatories, analgesics, and anti-gas drugs) with the same intake interval; absence of neurological or musculoskeletal disorders or alterations; and not physically active.

Exclusion criteria will encompass discontinuation of TENS or the LLLT photobiomodulation interventions; failure to perform the 2-min walk test (2MWT) during the assessment period; presence of clinical or obstetric instability during the assessment period; or patients who have already undergone TENS intervention or have a cognitive deficit.

The sample will be randomized (www.randomization.com) in four groups: TENS intervention combined with LLLT photobiomodulation, TENS alone, placebo, and control. The groups will be coded, and allocation will be done in sealed and opaque envelopes, numbered consecutively.

This study will have three investigators: the first will be responsible for randomization, the second for assessments, and the third for delivering the intervention. This will be a blinded study because the second investigator and the patients will be unaware of the allocation and intervention.

This protocol was approved by the research ethics committee of the Federal University of Rio Grande do Norte (Brazil) (CAAE: 53263721.5.0000.5537) and submitted to the Brazilian Registry of Clinical Trials (RBR-9pjd2n3). The autonomy and anonymity of patients will be respected, and personal data privacy will be ensured following resolution no. 510/16 of the National Health Council and the Declaration of Helsinki. Before entering the study, all patients will sign the informed consent form for written. The flow chart of study protocol is described in Fig 1 (Fig 1).

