**Fig 1 pone.0325254.g001:**
[figure not shown]
Flow chart of study protocol. Flow chart of study protocol. CONSORT 2010 FLOW DIAGRAM.

Our study followed the standard protocol items: recommendations for interventional trials (SPIRIT), which aims to improve clinical trial quality (S1 Checklist, SPIRIT 2013 Checklist) *.

The patients included will be evaluated at three time points: t1 (8–12 h post-cesarean) will use an evaluation form, International Physical Activity Questionnaire (IPAQ) application, pain intensity, pressure pain tolerance and threshold, functional capacity, and cardiorespiratory physiological variables evaluation; t2 (20–24 h post-cesarean) and t3 (44–48 h post-cesarean) will evaluate pain intensity, pressure pain tolerance and threshold, functional capacity, and cardiorespiratory physiological variables.

After t1 and t2, patients allocated to intervention groups will receive their respective protocol.

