### Cesarean incision pain

In assessments 1, 2, and 3, the NPS and digital algometer will assess pain in the cesarean incision region.

Pain intensity will be assessed using the NPS [9,15]. This scale allows the patient to classify pain from level 0 (no pain) to level 10 (extreme pain). The evaluation of pain will follow verbal descriptors (0 = no pain; 1–3 = mild pain; 4–6 = moderate pain; and 7–10 = extreme pain). Pain in the abdominal region will be assessed with the patient at rest and in movement (one minute after the 2MWT).

Pressure pain tolerance and threshold will be assessed by a digital force gage algometer (WAGNER FDM model), a device with a 1 cm^2^ rubber disc connected to a pressure gauge, which displays values in kgf/cm^2^ [9]. The patient will be instructed to say “started” when the pressure applied by the device begins to evoke pain (threshold), and the pressure will continue until the patient says “stop” (tolerance). The pressure will be applied perpendicularly at the midpoint between the navel and the cesarian incision, taking the linea alba as a reference. The rubber disc will be covered with plastic film and cleaned with 70% alcohol before each patient.

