**Fig 3 pone.0325254.g003:**
[figure not shown]
TENS combined with LLLT photobiomodulation. a: cesarean incision; b: TENS channel 1; c: TENS channel 2; d: LLLT photobiomodulation; e: electrode (size 5 x 3 cm).

Protocol for TENS alone: patients will receive the same TENS intervention parameters and positioning previously described in the TENS combined with LLLT photobiomodulation protocol.

Protocol for the placebo: Patients will follow the same TENS combined with LLLT photobiomodulation protocol as in the intervention group, but the equipment will not emit light or electric current.

Protocol for the control: Patients will only undergo t1, t2, and t3.

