### Statistical analysis

Data analysis will be performed using SPSS software version 22.0 (IBM Corp. USA), and in all statistical analyses, p values < 0.05 were considered as statistically significant. Will be performed Shapiro-Wilk test and Levene for normality of the data distribution and equality of variances. Descriptive statistics will be presented using the measures of central tendency. Mauchly’s test of sphericity will be used to validate the correlation of the repeated measures, and if the assumption of sphericity was violated, the Greenhouse-Geisser correction will be applied. Two-way repeated measures ANOVA will be to compare the effects of TENS combined with LLLT photobiomodulation between groups (TENS alone, Placebo and Control) over time (assessment t1, t2 and t3) on a primary outcome (pain) and secondary outcomes (functional capacity, systemic arterial pressure, respiratory and heart rates, oxygen saturation and Functional Independence Measure). When appropriate, post hoc comparisons will be carried out using Tukey’s post hoc correction for multiple comparisons. The effect size will be calculated by Cohen’s. For the missing data, intention to treat analysis will be used.

For better data management and quality control the investigator responsible for randomization will be responsible for organization the collected patients information in spreadsheets and ensure confidentiality without personal identification of the research participants.

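### The exclusion criteria remove women for events after allocation, which contradicts the stated intention-to-treat analysis and can bias the comparison in either direction

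*Protocol article*

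**What the plan says.** Among the exclusion criteria (Materials and methods), next to true baseline conditions such as previous TENS and cognitive deficit, stand three that describe events during the study: "Exclusion criteria will encompass discontinuation of TENS or the LLLT photobiomodulation interventions; failure to perform the 2-min walk test (2MWT) during the assessment period", and then "presence of clinical or obstetric instability during the assessment period".

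The assessment period has three time points, t1, t2 and t3. The text with the flow chart places treatment between them: "After t1 and t2, patients allocated to intervention groups will receive their respective protocol". Under Intervention protocols, control women have no device ("Patients will only undergo t1, t2, and t3"). Placebo women go through the combined session, "but the equipment will not emit light or electric current".

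Under Statistical analysis the article says: "For the missing data, intention to treat analysis will be used". That is its only mention of the principle. It does not say that an excluded woman stays in follow-up or in the analysis.

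**The concern.** An intention-to-treat analysis compares women as randomised, whatever happens to them afterwards. A rule that excludes them for what happens afterwards is its opposite, and both are written into the same article.

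Two features make this more than loose wording. First, one criterion has no counterpart in the control arm, because a woman without a device cannot stop using it. Second, the other two criteria overlap with what the trial measures. The 2MWT is the functional capacity outcome. Movement pain also depends on it: "Pain in the abdominal region will be assessed with the patient at rest and in movement (one minute after the 2MWT". Instability is close to the cardiorespiratory outcomes and to possible harms. Exclusion on an event related to the outcome can leave groups that are no longer comparable, and if t2 and t3 data are not collected from an excluded woman, no later analysis can recover them.

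**Working it through.** **1. When can each event occur, and in which arms?** Sessions follow t1 and t2.

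| Criterion | Timing | Arms it can affect |
|---|---|---|
| Stopping TENS or LLLT | Always after allocation | Combined, TENS alone, placebo; not control |
| Failing the 2MWT | t1, t2 or t3; at t2 and t3 after treatment has started | All four |
| Clinical or obstetric instability | t1, t2 or t3; at t2 and t3 after treatment has started | All four |

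The article says "The sample will be randomized (www.randomization.com) in four groups" but does not say whether the envelope is opened before or after t1. Events at t1 may therefore precede allocation. Those at t2 and t3 cannot.

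**2. The plan's own figure.** The sample size allows for losses: 17/(1 − 0.20) = 21.25, rounded up to 22 per group, and 4 × 22 = 88. This step reproduces. It leaves room to lose 5 of 22 women per group (22.7%), or 20 of 88.

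**3. Is lost power the problem?** Take the article's 2-point difference and SD of 1.5, with two-sided alpha of 0.05 (sidedness is not stated, so this is assumed). For one pair of groups, by the normal approximation, power = Φ(2/(1.5 × √(2/n)) − 1.96).
- n = 22: Φ(4.42 − 1.96) = 99.3%.
- n = 17: Φ(3.89 − 1.96) = 97.3%.

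Power hardly moves. The harm to look for is bias.

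**4. How large could the bias be?** The article gives no exclusion rates and no link between exclusion and pain, so both are assumed. Suppose there is no true effect, the SD is 1.5, and a share d of an arm is excluded through a mechanism correlated ρ with pain. The mean of those retained then falls by ρ × 1.5 × φ(z)/(1 − d), where z is the normal quantile at 1 − d.
- d = 20%: 1.5 × 0.280/0.80 = 0.525. With ρ = 0.3, 0.5 and 0.8 the fall is 0.16, 0.26 and 0.42 points.
- d = 5%: 1.5 × 0.103/0.95 = 0.163. With ρ = 0.3 and 0.8 the fall is 0.05 and 0.13 points.

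A simulation of two arms of 22 under the same assumptions (10,000 runs per setting, t-test) gave:

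| Excluded, arm A vs arm B | Shift in mean pain, ρ = 0.3 to 0.8 | Two-sided type I error |
|---|---|---|
| 20% vs 0% | 0.16 to 0.42 | 6% to 14% |
| 20% vs 5% | 0.10 to 0.29 | 5% to 9% |
| 20% vs 20%, same mechanism | 0 | about 5% |

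Against the planned 2-point effect, 0.16 to 0.42 is 8% to 21%. The sign depends on which arm is A. More exclusion in an active arm flatters the intervention, and more exclusion in control or placebo works against it.

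**The case against.** The best defence is that the article names intention to treat, that a fuller protocol or SAP may define an analysis set that keeps these women, and that a CONSORT flow diagram is referred to, so exclusions may well be reported. This stands in part. The article does not prove that a per-protocol analysis will be run or that tolerability problems will be hidden, and a reader should not infer either. The conflict remains, because the written rule excludes these women and the single sentence on intention to treat concerns missing data and does not restore them.

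Three other stronger readings are tempting and not supported:
- **That all three events can only follow allocation.** This is true of stopping the device. Walk-test failure and instability can also occur at t1, possibly before the envelope is opened.
- **That all three criteria remove women unequally by arm.** Control women undergo every assessment, so two of the three apply to them as well. Placebo and TENS-alone women also have a device session to stop. Built-in asymmetry is shown only for discontinuation, against control.
- **That the bias favours the intervention.** If treatment relieves pain, more untreated women might fail the walk test, and excluding them would remove high-pain women from control and placebo. The 20% loss allowance does not settle this, since it applies to every group and to losses in general.

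**Conclusion.** The point holds as a contradiction between the exclusion criteria and the analysis principle, and that part needs no assumption. Followed as written, the rule breaks the randomised comparison for the primary outcome.

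Whether it biases the result, by how much and in which direction cannot be read from the article. On assumed rates the range runs from no bias (equal rates, same mechanism) to about 0.2 to 0.4 NPS points (20% against none, correlation with pain 0.3 to 0.8). These figures illustrate and do not predict. The 20% loss allowance protects power and does nothing for comparability.

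**What to change.** Reconcile the exclusion criteria with the Statistical analysis section:

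- Limit exclusion criteria to conditions present before allocation, and say when the envelope is opened relative to t1.
- State that women who stop the device, cannot do the 2MWT at t2 or t3, or become unstable remain in their randomised arm for follow-up and analysis. This is separate from any clinical decision about continuing treatment, which the amendment need not touch. Resting NPS and other feasible measures are still collected.
- Record an inability to walk, with its reason, as an outcome.
- Prespecify how missing 2MWT distance and missing movement pain are handled. Scoring a failed walk as 0 m is one option, but a debatable one, since it puts extreme values into the planned ANOVA, and it leaves movement pain unresolved.
- Report discontinuation, walk-test failure and instability by arm.
- Restore women already excluded under the present rule with whatever data exist. Recruitment began in July 2023 and data collection was expected to end in August 2025, so for some women only this last step and the reporting can help.

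The cost is a wording amendment and a little more follow-up and analysis work. The sample size stays at 88.

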### Intervention protocols

Protocol for TENS combined with LLLT photobiomodulation: Both interventions will be applied simultaneously, with the patient positioned in the supine position and a neutral posture. We will follow a TENS intervention protocol previously described [1], consisting of low-intensity TENS (30 min, 100 Hz, and 75 µs) applied using two channels and four electrodes (size 5 x 3 cm) placed in the skin surface with conductive gel above and below the cesarean incision, sanitized with 70% alcohol. The LLLT photobiomodulation intervention protocol will follow a reference from the literature [9], consisting of 660 nm (red), energy of 2 J per point, and power of 100 mW, performed in two sessions without skin contact in the cesarean incision. The LLLT intervention will be punctual and applied perpendicularly to the skin surface in the line of the cesarean incision [8]. The number of points applied will depend on the extent of the cesarean incision. The time per point will be 20 seconds, and the distance of 1 cm between application points will be respected. To perform the application with LLLT photobiomodulation, the application pen will be cleaned with 70% alcohol before each patient. Asepsis in the cesarean incision region will also be performed using 70% alcohol before and after the intervention. Only the therapist and the patient will be present during this application due to the need for specific protective glasses for the LLLT. The Fig 3 represent the procedure to application TENS combined with LLLT photobiomodulation.

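### Patients are said to be blinded, but control women get no procedure and no sham laser is described for TENS alone, so combined versus TENS alone is not procedure-matched on patient-reported pain

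*Protocol article*

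**What the plan says.** Under Materials and methods, one investigator randomises, a second assesses and a third treats. The article then states: "This will be a blinded study because the second investigator and the patients will be unaware of the allocation and intervention".

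Intervention protocols describes the four arms:

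- **Combined:** "Both interventions will be applied simultaneously, with the patient positioned in the supine position and a neutral posture". A laser pen is applied point by point along the incision. Only therapist and patient are present, "due to the need for specific protective glasses for the LLLT".
- **TENS alone:** "patients will receive the same TENS intervention parameters and positioning previously described in the TENS combined with LLLT photobiomodulation protocol". The abstract agrees: "The TENS alone group will follow the same low-intensity TENS protocol used in the combined intervention".
- **Placebo:** the combined procedure, "but the equipment will not emit light or electric current".
- **Control:** "Patients will only undergo t1, t2, and t3".

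The abstract gives two aims: to evaluate the combination, and to compare it with TENS alone. The primary outcome is pain. The patient rates it on a 0–10 scale, and the algometer readings also depend on when she says that pain starts and when to stop.

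**The concern.** A woman who receives no device knows that she receives no intervention. A woman given electrodes but no laser pen undergoes a visibly different session from one given both. Patient blinding across all four arms is therefore claimed but not built into the procedures.

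Two things are at stake. The first is accuracy: a report repeating the blinding sentence would credit the trial with a safeguard that it lacks for some contrasts. The second is interpretation. If the combination beats TENS alone, readers will want to know whether photobiomodulation did it, and without a sham laser in the TENS-alone arm that difference cannot show it. Assessor blinding does not help, because the assessor records what the patient reports.

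**Working it through.** The plan gives no figure on this point, so there is none to reproduce. The check has three steps.

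**1. Visible procedure by arm**

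| Arm | TENS electrodes | Laser pen along incision | Can the patient be unaware? |
|---|---|---|---|
| Combined | active | active | yes, relative to placebo |
| Placebo | inactive | inactive | yes, relative to combined, unless lack of sensation gives it away |
| TENS alone | active | none described | not matched to any other arm |
| Control | none | none | no |

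Only one of the six pairs, combined and placebo, shares the same visible procedure.

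**2. What each contrast estimates**

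Write m for the control mean, S_T and S_L for the specific effects of TENS and laser, and E_T and E_L for the expectation effects of the two visible procedures. Assume that effects add and that the sham is not recognised.

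- Control: m
- TENS alone: m + S_T + E_T
- Combined: m + S_T + E_T + S_L + E_L
- Placebo: m + E_T + E_L

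Then:

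- Combined − TENS alone = S_L + E_L
- Combined − placebo = S_T + S_L
- Placebo − control = E_T + E_L

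There are four means and five unknowns. Raise S_T and E_L by any amount c and lower E_T and S_L by c, and all four means are unchanged. For example, combined changes by c − c − c + c = 0. So no combination of the four arms isolates S_L. With an inactive laser in the TENS-alone arm, that mean becomes m + S_T + E_T + E_L, and combined minus TENS alone equals S_L.

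**3. Illustration of the consequence**

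Inputs from Materials and methods: SD 1.5 per group, alpha 0.05 (taken as two-sided), 17 per group before and 22 after the allowance for losses. Assumed: S_L = 0, and E_L between 0.25 and 1.0 points.

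Standard error of a difference = 1.5 × √(2/n), which is 0.51 for n = 17 and 0.45 for n = 22. The chance of a significant difference comes from the noncentral t distribution with 2n − 2 degrees of freedom and noncentrality E_L divided by the standard error.

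| Assumed E_L (points) | n = 17 | n = 22 |
|---|---|---|
| 0 | 5% | 5% |
| 0.25 | 8% | 8% |
| 0.5 | 16% | 19% |
| 0.75 | 29% | 37% |
| 1.0 | 47% | 58% |

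This is an unadjusted two-group t-test. The planned analysis is a repeated-measures ANOVA with Tukey comparisons, so actual figures would differ, and the Tukey adjustment alone would lower them. The bias itself equals E_L whatever the sample size.

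**The case against.** **The absence of a sham laser is inferred.** An article condenses, and this arm gets one sentence. It is true that the text nowhere says TENS-alone women get no pen or glasses, and the glasses are mentioned only to explain who is in the room. What women are told about the arms is also not shown. The correct wording is therefore that none is described. The inference is still a fair one, because the sham is spelled out for placebo and the abstract also gives TENS alone only the TENS protocol. For control no inference is needed.

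**Blinding does not fail everywhere.** A reader might infer that patient blinding is impossible throughout. The documents do not support that. Placebo follows the combined procedure, and women who have already had TENS are excluded, so they have no earlier sensation to compare with. Recognition remains possible, since the Introduction describes the cited TENS trial as using a sensory-threshold intensity and the present TENS protocol follows it.

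**The aim may be pragmatic.** The primary objective concerns the combination and does not name TENS alone, and the article nowhere says that a difference will be credited to the laser light alone. This stands: a comparison of packages is legitimate if it is called that.

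**Placebo versus control could serve as a correction.** It estimates only the sum over both devices. At 22 per group its 95% half-width is about 1.96 × 0.45 = 0.9 points. It gives context but cannot be subtracted to recover the laser effect.

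**The size is unknown.** It is tempting to express an assumed expectation effect as a share of the 2-point reduction in the sample-size text. That text does not tie the 2 points to combined versus TENS alone, so such a percentage would have no basis. TENS-alone women also receive a 30-minute device session, so only the added expectation from the laser counts.

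**Conclusion.** The blinding statement is wrong as written for patients. This is certain for control and follows for TENS alone from the procedures described. Assessor blinding is not contradicted. Combined versus placebo is procedure-matched and serves the primary objective, but it cannot separate laser from TENS. Combined versus TENS alone mixes the specific laser effect with the expectation effect of a visible extra procedure, and no other contrast among the four arms separates the two.

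The size of the expectation effect cannot be derived from the documents. The 8% to 58% range above is an illustration that rests on assumed effects of 0.25 to 1.0 points. The contradiction and the limit on attribution do not depend on it.

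A reader might infer that attribution to the laser could be rescued by relying on sham-matched contrasts. It cannot for women treated as now described, because the only matched contrast estimates TENS and laser together.

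**What to change.** 1. **Correct the statement and the interpretation now.** Replace the blinding sentence with: *assessor-blinded; patients not blinded in the control arm; procedure-matched only between combined and placebo*. Describe contrasts with control as open-label. Report combined versus TENS alone as a comparison of treatment packages whose difference cannot be attributed to photobiomodulation alone. If a sham laser is in fact used with TENS alone, say so instead and adjust the wording. The cost is wording and a less favourable blinding description.

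2. **If enough women remain to be randomised, add the sham.** Use the placebo arm's inactive laser procedure, with its pen and glasses, in the TENS-alone arm, and report results before and after the change. Recruitment began in July 2023, and data collection was expected to end in August 2025. The number still to be randomised is not given, so this may no longer be worthwhile. At 20 s per point and 1 cm spacing, an assumed 10–15 cm incision needs about 10–15 points, or 200–300 s (roughly 3–5 minutes), which fits within the 30-minute TENS session. No new device or staff are needed. The cost is an amendment, those few minutes, and two delivery versions of an arm of 22. Women already treated stay under item 1.
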